**Figure 1 F1:**
[figure not shown]
Weight vest.

#### Training volume

Except for the relax station, which served as a relax moment, each station had its own training volume (i.e. a combination of load, repetitions, sets and rest) with which the exercise was performed.

As is shown in Table 2, the choice of a training volume is directly related to the desired goal of muscle training, and to achieve enhanced muscle strength, the training must be based on a fixed combination of a high load (70–95% 1 RM), 8–12 repetitions, 1–3 sets and sufficient rest to allow for muscle recovery. In this study we focussed on the improvement of both strength and strength/endurance training, and therefore used a high to low load and a low to medium number of repetitions. Table 3 presents the training volumes of the exercises at the different stations. All exercises were performed in 3 sets of 8 repetitions, with a 90 second rest in between the sets. Each exercise was performed within 7–10 minutes. At the beginning of each new training session, every child started at one of the 5 stations, from which he/she rotated to the next, until he/she had completed 4 stations (see Figure 2). At the beginning of each subsequent training session, the child started at a different station. Consequently, each station was completed, i.e. each exercise was performed, 2 to 3 times a week.

**Table 2 T2:** Different training volumes, related to the desired goal of muscle training (after Wilmore & Costill Physiology of Sport and Exercise)

**Training goal**	**Training volume **			
	***Load (% 1 RM)***	***Repetitions***	***Sets***	***Rest between sets***
Maximum strength training	95–100%	1–3	1–3	2–4 min
(Sub-maximal) strength training	70–95%	8–12	1–3	90–120 sec
Strength endurance training	50–70%	10–15	1–3	45–90 sec
Endurance training	<50%	20–50	3–5	<45 sec
Co-ordination training	<30%	30–70	4–6	<45 sec

Abbreviation: RM = Repetition Maximum

**Table 3 T3:** Training volumes of progressive resistance exercise

**Station**	**Training volume **			
	***Maximum Load***	***Repetitions***	***Sets***	***Rest***
1. Leg-press	100% 8 RM	8	3	90 sec
2. Loaded sit-to-stand	75% 8 RM	8	3	90 sec
3. Loaded game	25% 8 RM	8	3	90 sec
4. Unloaded game	body weight	8	3	90 sec
5. Relax	n.a.	n.a.	n.a.	n.a.

Abbreviation: RM = Repetition Maximum, n.a. = not applicable

**Figure 2 F2:**
[figure not shown]
**The 5-station circuit**. During one training session, in which a maximum of 5 children participated, each child started at one of the 5 stations, and rotated through the circuit until 4 exercises had been completed.

After each training session the physical therapist recorded the type of exercise performed, with the number of repetitions and sets, and the training load in a child-specific diary. Any adaptations made to the training were also recorded, as well as any muscle soreness or any other lower limb pain that the child had possibly experienced.

#### Training load and 8 Repetition Maximum

The training load for the exercises was established according to the individual 8 RM test. The 8 RM is approximately equal to 80% 1 RM[23] (N.B.: the 1 RM test was considered to be too heavy). The 8 RM test procedures were initiated after the children had become familiar with the training program, and when they could perform the exercises correctly. To determine the 8 RM, the child started with 3 repetitions (no load) to practise the correct performance: each repetition had to be performed through full (possible) range of motion, with adequate speed (speed of repetition: extension movement: 2–3 seconds/flexion movement: 2–3 seconds[6]). Then, two warm-up trials of 3 repetitions were performed at 50% and 70% of the predicted 8 RM, respectively. The predicted 8 RM is based on the child's body weight, according to GMFCS-specific guidelines which we established in an earlier pilot study (see Table 4). After the third and actual test trial, the child was instructed to perform the trial at 100% of the predicted 8 RM until (temporary) muscular exhaustion, or until a maximum of 10 repetitions. If a repetition was performed incorrectly, it was not counted; and if two consecutive repetitions were performed incorrectly, the trial was ended. The criteria for incorrect technique were: without full (possible) range of motion, with incorrect technique and inadequate speed (i.e. too slow/fast). If a child performed less than 6 or more than 10 correct repetitions, a 5 to 10% load was either reduced or added, respectively. After a 3 minute rest, the trial was repeated until the child was able to perform 7–9 repetitions, but no more.

**Table 4 T4:** Guidelines for the predicted 8 repetition maximum

**Station**	**GMFCS level**	**Predicted 8 RM**
1. Leg-press	I	120% of the body weight
	II	100% of the body weight
	III	80% of the body weight
2. Loaded sit-to-stand	I	35% of the body weight
	II	30% of the body weight
	III	25% of the body weight

Abbreviations: GMFCS = Gross Motor Function Classification System; RM = Repetition Maximum

RM test procedures are known to be labour-intensive and time-consuming, and to require close and experienced supervision[19]. Therefore, we could not perform these tests for every exercise on a regular basis. We chose to regularly determine the 8 RM for the leg-press[24] (i.e. weeks 3, 6, 8 and 10) (see Additional file 5), but the 8 RM for the loaded sit-to-stand[25] was only tested twice (i.e. weeks 4 and 9). In two other weeks (7 and 11) the training load for the loaded sit-to-stand was estimated based on the progress in 8 RM testing on the leg-press between weeks 3 and 6 and weeks 8 and 10, respectively (see Additional File 5), which was set at a minimum of 0% and a maximum of 10%. No 8 RM test was determined for the loaded game exercises. The load for these exercises was estimated with the 8 RM test for the loaded sit-to-stand (see Additional File 5).

Two types of loading or resistance materials were used: the leg-press with a weight range from 5 to 200 kg, adjustable in 1 kg steps, and a weight vest (see Figure 1) with weight bags in different weights, ranging from 0.5 kg – 3 kg. The load in the weight vest was always equally divided between the front and the back and between the left and right side.

Each exercise had its own maximum training load (see also Table 3): the leg-press and loaded sit-to-stand exercises were performed at a maximum of 100% 8 RM and 75% 8 RM, respectively, the loaded game at 25% 8 RM, and the unloaded game with no extra resistance except body weight. These training loads were adjusted to new individual levels of strength, if necessary (i.e. as determined by the 8 RM test). The first 6 weeks were intended to slowly build up the training towards these maximum training loads and during the last 6 weeks the children were training at the maximum load. The exact training loads and timing of 8 RM tests per exercise per week are presented in Additional File 5.

### Outcome measures

The data were collected in each of the participating schools by two blinded, independent research assistants. One pre- (T0) and three post-training assessments were made (T 1/2: after 6 weeks of training, T1: at the end of the training, T2: 6 weeks after the end of the training). The T0, T1 and T2 assessments were scheduled during a two-week period and the T 1/2 assessment was scheduled during a one week period. Measurements of the height and weight of the children were obtained during each session, as well as the type of shoes they wore and the type of orthosis or walking aid they used.

The outcome measurements in this study include assessments of the body function and structure, and activity and participation at ICF level (see Figure 3). The primary outcomes were gross motor function and walking ability (activity level), and the secondary outcomes were muscle strength (body function and structure level), mobility (activity level) and sport activities (participation level). In addition, various personal characteristics were measured once at baseline, in order to control for possible age, gender and gross motor function differences, as well as for emotional or behavioural problems (measured with the Strength and Difficulties Questionnaire [SDQ][26]) and degree of sexual maturation (based on the Tanner score[27]).

**Figure 3 F3:**
[figure not shown]
**Study outcomes and instruments used on the different ICF levels**. * primary outcomes; ^† ^secondary outcomes; ^§ ^adverse outcomes; ^‡ ^control outcomes. Abbreviations: CP = Cerebral Palsy, GMFM = Gross Motor Function Measure, CAPE = Children's Assessment of Participation and Enjoyment, MobQues = Mobility Questionnaire, GMFCS = Gross Motor Function Classification System, SDQ = Strength and Difficulties Questionnaire

### Primary outcome measures

#### Gross Motor Function

*The Gross Motor Function Measure (GMFM) *is a standardized observational measurement instrument that requires a child to demonstrate various motor skills, as outlined in the GMFM administration and scoring guidelines. Consequently, it reports on the child's actual level of ability. It has been validated for evaluating change in the gross motor activities of children with CP. In this study we used the 66-item version of the GMFM (GMFM-66), an internationally recognised valid and reliable outcome measure, based on interval scaling[28].

*Functional muscle strength *was measured with two different functional exercises in which the large muscle groups that are important in daily activities were assessed: the 30-s Lateral Step-Up Test[29] and the 30-s Sit-to-stand Test[29].

The 30-s Lateral Step-Up Test[29] assesses the number of step ups that the child can perform in 30 seconds. The test was performed on a 21 cm (GMFCS I and II) or an 11 cm (GMFCS III) step. The child stood next to the step and put the more impaired (i.e. tested) leg on the step, where it remained throughout the entire test. The child was asked to lift his/her less or un-impaired (i.e. non-tested) leg up and put it on the step, by fully extending the hip and knee of the tested leg. After this, he/she set the non-tested leg back on the ground, next to the step. A full movement (stepping up and down) was counted as one repetition.

The 30-s Sit-to-Stand Test[29] assesses the number of sit-to-stands that the child can perform in 30 seconds. The test was performed on a child-sized chair with a height-adaptable seat (no backrest, no armrest). The upper legs were parallel to the floor, the feet parallel on the ground (as flat as possible) and the trunk erect. The child was asked to stand up, as erect as possible with symmetric hip strategy ("flex hips and move trunk forward until the shoulders are above the knee joint and then stand up"). A full movement (standing up and sitting down) was counted as one correct repetition.

#### Walking ability

*The Timed 10-Meter Walk test (10 MWT) *assessed the time (in seconds) and number of footsteps needed to walk 10 meters. The 10 MWT test was performed on a 14 meter straight, flat, smooth, non-slippery walking surface. The child was instructed to walk at a self-selected comfortable speed. The test was performed with a 'flying start' (i.e., while the child walked approximately 14 meters, the time and number of footsteps for walking the intermediate 10 meters were measured). From this, cadence, step-length and comfortable walking velocity were calculated.

*The 1-Minute Walk Test*[30]*(1 MWT) *assesses the distance (in meters) walked during 1 minute. The 1 MWT test was performed on a 20–22 m figure of eight-shaped, flat, smooth, non-slippery oval walking track. The child was instructed to walk around the track for 1 minute at his/her fastest attainable speed (no running). During this test the distance (in meters) was calculated to the nearest meter by means of self-attached meter marks on the track, to calculate fast walking speed.

*The Timed Stair Test (TST) *assesses the time needed to go up and down stairs[15]. The test was performed on a 4 or 5-step set of stairs, with handrails on both sides. The child started at the bottom of the stairs, and was instructed to walk up the stairs as fast as possible, without running, and with alternating feet if possible (if not: step with both feet on the same step), then turn round on the platform and walk down the stairs, with alternating feet if possible (if not: step with both feet on the same step).

### Secondary outcome measures

#### Muscle strength

#### 

*6 RM muscle strength.* The strength of the major muscles of the lower body, as a percentage of body weight, was measured with a 6 RM test on a leg-press. This test was chosen as an outcome measure instead of the 8 RM test, as a slight modification of the training exercise (N.B.: the 1 RM test was considered to be too heavy). The 6 RM test was performed in the same way as the 8 RM test described in the Methods section, except that the child was instructed to perform the third trial at 100% of the predicted 6 RM until temporary muscular exhaustion, or until a maximum of 8 repetitions (range 5–7). Based on an earlier pilot study, the initial leg-press load for the 6 RM was estimated at 130%, 110% and 90% of body weight for children with levels GMFCS I, II and III, respectively.

#### 

*Isometric strength tests*. The isometric muscle strength of the unilateral hip flexor/abductor, knee flexor/extensor, and ankle plantarflexor muscles were measured with a hand-held dynamometer (MicroFet, Biometrics, Almere)[15,31]. A "make" test was performed, in which the investigator stabilized the dynamometer, while the child pushed as hard as possible against the dynamometer for a period of 3 seconds, during which the peak force (in Newton) was assessed. The mean scores of three tests were used for the analysis. A standardized protocol was used for positioning of the child, joint fixation, joint positioning and dynamometer resistance (see Table 5).

**Table 5 T5:** Isometric muscle strength testing: protocol for child positioning, joint fixation, joint positioning and dynamometer resistance

**Muscle group**	**Child position**	**Joint fixation**	**Joint starting position**	**Position of dynamometer resistance**
Knee extensors	Sitting	Pelvis and thigh	Knee flexed 90°	Anterior tibia, 5 cm proximal to malleoli
Knee flexors	Sitting	Pelvis and thigh	Knee flexed 90°	Posterior calf, 5 cm proximal to malleoli
Hip flexors	Sitting	Pelvis	Hip flexed off surface	Anterior thigh, 3 cm proximal to patella
Hip abductors	Supine	Pelvis	Hip slightly flexed off surface using a knee roll	Lateral thigh, 5 cm proximal to the knee joint
Ankle plantarflexors	Supine	Pelvis and lower leg	Hip flexed 90°, lower leg stabilized on a bench, ankle in neutral position.	Plantar surface of foot, across metatarsal heads

Abbreviation: cm = centimeter

#### 

*Anaerobic power*. The anaerobic sprint power output of the legs was evaluated during a 20-second full out cycle-test (adapted from the original 30-second test)[32]. It was performed on a child-adapted cycle-ergometer (Corival, Lode bv, Groningen). After a warming-up period of 5 minutes (cycling at low resistance, interspersed with three 5-second sprints), the child was asked to cycle as fast as possible for 20 seconds (sprint) against a constant force. Two performance indices were calculated (mean and peak power) with specialized software (ProCare bv, Groningen). The former reflects the child's ability to sustain high power, whereas the latter indicates the ability to produce high mechanical power in a short time. These outcomes are considered to be closely related to the short-term energy system that is employed to perform daily tasks in children with CP[32].

#### Mobility

*The Mobility Questionnaire (MobQues) *is a Dutch questionnaire that measures mobility limitations based on 47 caregiver-reported items. These concern the mobility tasks of every day life, which include both indoor and outdoor activities such as 'sit down on a chair', 'go up stairs', and 'walk on asphalt'. One of the child's parents or caregivers was asked to complete the MobQues, and to indicate how difficult it was for their child to perform these mobility tasks in the usual way (with the use of assistive devices if needed) without any help from others. The response options, given on a 5-point scale, were: not difficult at all, slightly difficult, somewhat difficult, very difficult, impossible without help. In this study we used the 28-item version of (MobQues-28), which is based on interval scaling. The MobQues-47 and MobQues-28 were found valid and reliable according to a recent study that was performed in a Dutch population, which results' will be published in the near future.

#### Sport activities

*The Children's Assessment of Participation and Enjoyment (CAPE)*[33] measures the child's participation in every day activities, outside of the school program. It is completed by the parents or caregivers, together with the child. For the present study, 17 items were chosen from the sub-scales of physical (items 32, 36), recreational (items 16, 20, 21, 33–35, 37–41) and skill-based (items 17–19) activities as outcome measures, because these items measure the frequency of participation in 17 different sport activities. For each of these activities the child was asked whether, and if so, how often he/she had participated in this activity in the previous 4 months.

### Adverse outcomes

*The Range f Motion *in the hamstrings, adductors, rectus femoris, soleus and gastrocnemius muscles was assessed with goniometry during the third of three slow passive stretches (>3 seconds)[34].

#### 

*Spasticity*. Goniometry was also used to measure spasticity in the hamstrings, adductors, rectus femoris, soleus and gastrocnemius muscles by assessing the joint angle at which a 'catch' (defined as a sudden increase in muscle tone, blocking further movement) occurred in a fast passive stretch (<1 second)[35].

### Data-analyses

Student T-tests (continuous data, if normally distributed), Mann-Whitney tests (continuous data, if not normally distributed), and Chi-square tests (dichotomous and ordinal data) will be used to evaluate group differences at baseline. Differences in change from baseline between the intervention group and control group for the three post baseline assessments will be evaluated by means of generalized estimating equations (GEE) for longitudinal analysis[36]. GEE is appropriate for analyzing longitudinal data with hierarchically structured data and the advantage of GEE is that this method takes into account the dependency of repeated measures within the same person. To determine the effect of the strength training program, changes in the training group will be compared to the changes in the control group (interaction between group * time).

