**Methods/Results:**

Fifty-one children with Gross Motor Function Classification Systems levels I to III, aged of 6 to 13 years, were recruited. Using stratified randomization, each child was assigned to an intervention group (strength training) or a control group (usual care). The strength training was given in groups of 4–5 children, 3 times a week, for a period of 12 weeks. Each training session focussed on four exercises out of a 5-exercise circuit. The training load was gradually increased based on the child's maximum level of strength, as determined by the 8 Repetition Maximum (8 RM). To evaluate the effectiveness of the training, all children were evaluated before, during, directly after, and 6 weeks after the intervention period. Primary outcomes in this study were gross motor function (measured with the Gross Motor Function Measure and functional muscle strength tests) and walking ability (measured with the 10-meter, the 1-minute and the timed stair test). Secondary outcomes were lower limb muscle strength (measured with a 6 RM test, isometric strength tests, and a sprint capacity test), mobility (measured with a mobility questionnaire), and sport activities (measured with the Children's Assessment of Participation and Enjoyment). Spasticity and range of motion were assessed to evaluate any adverse events.

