### Sample size

At least 42 children were required to detect a difference in improvement of 5% on the Gross Motor Function Measure (GMFM) between the intervention group and the control group, with a power of 0.8 and an alpha of 0.05. To allow for some drop-outs, we aimed to recruit at least 50 children (25 intervention, 25 control).

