#### Circuit training

The training sessions were held in small groups (± 4–5 children) with a 5-station circuit, supervised by two experienced physical therapists per group. During each training session, the children wore their regular (street) shoes, splints, trousers, and they all wore a group T-shirt to stimulate the group-feeling. Each training session started and finished with a warming up and cooling down period of 5–10 minutes, during which muscle stretching exercises and aerobics were performed. During the main training phase, each child performed 4 different exercises on the 5-station circuit. The different stations of the circuit were named as followed: leg-press, loaded sit-to-stand, loaded game, unloaded game and relax. Table 1 presents the characteristics of the 5-station circuit.

**Table 1 T1:** Characteristics and training volumes of the 5-station circuit

**Station**	**Load**	**Trained Leg**	**Exercise**	**Functional**	**Supervision**	**Game**	**Resistance**
1. Leg-press	High	Bilateral	Leg-press	No	Very strict	No	Leg-press
2. Loaded sit-to-stand	High	Bilateral	Sit-to-stand	Yes	Very strict	No	Weight vest
3. Loaded game	Low	Unilateral	Half-knee rise; Lateral step up; Forward step up; (Sit-to-stand)	Yes	Strict	Yes	Weight vest
4. Unloaded game	No	Unilateral	Half-knee rise; Lateral step up; Forward step up; (Sit-to-stand)	Yes	Strict	Yes	Body weight
5. Relax	n.a.	n.a.	n.a.	n.a.	none	n.a.	n.a.

Abbreviation: n.a. = not applicable

The exercise stations were a combination of high load (e.g. leg-press and loaded sit-to-stand stations), low load (e.g. loaded game station) and no load (e.g. unloaded game station) exercises (see Table 1; the exercises are explained in more detail in Additional files 1 to 4).

At the stations that were highly loaded (e.g. leg-press and loaded sit-to-stand stations), both legs were trained simultaneously by means of bilateral exercises. The exercises at these stations were fixed: a leg-press exercise (see Additional file 1) and a loaded sit-to-stand exercise (see Additional file 2). Of these, only the loaded sit-to-stand is a functional exercise, resembling an everyday activity with which ambulatory children with CP may experience difficulty (i.e. rising from a chair).

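### The planned GEE names only within-child dependence, although one arm alone is trained in groups of 4–5; if outcomes correlate within training groups, the standard error of the training effect is too small

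*Protocol article*

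**What the plan says.** Protocol article, Data-analyses: differences between arms in change from baseline at the three later assessments are to be evaluated by GEE, with the training effect read from the group-by-time interaction. The section remarks in general terms that GEE suits data with a hierarchy. The one dependence it then names is that "this method takes into account the dependency of repeated measures within the same person". It mentions no training group, therapist or school level.

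Abstract, Methods/Results: "The strength training was given in groups of 4–5 children, 3 times a week, for a period of 12 weeks". The Circuit training section adds that sessions were "supervised by two experienced physical therapists per group". Controls received usual care and were not grouped in this way.

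Participants: children were randomised individually, separately within each of three schools.

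Sample size: 42 children are required for a 5% difference in GMFM improvement, "with a power of 0.8 and an alpha of 0.05". The step up to 50 has one stated reason: "To allow for some drop-outs, we aimed to recruit at least 50 children (25 intervention, 25 control". No standard deviation, ICC or design effect is given.

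**The concern.** Individual randomisation makes the children comparable at the start. It does not keep them independent afterwards if one arm is then treated in small groups. Children who share therapists, games, competition and group atmosphere over 12 weeks may improve or stall together. The article itself gives reason to expect this. The Background treats group delivery as something that raises motivation and effectiveness, and the Circuit training section describes a shared T-shirt meant to build group feeling. The result is a partially nested design: clustered in the intervention arm, unclustered in the control arm.

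Two separate things are at stake. First, an analysis that treats the intervention children as independent gives a standard error that is too small, so the type I error exceeds 5% and intervals are too narrow. Second, a sample size without a design effect gives less power than stated once the clustering is real. Understated standard errors cause the first problem but not the second.

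**Working it through.** **Inputs from the article.** Total 42 for power 0.8 at alpha 0.05 (two-sided assumed); difference 5 (reading the 5% as 5 GMFM points); target 25 + 25; training groups of 4–5.

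**Inputs assumed.** Within-group ICC of the change score, 0 to 0.20; mean group size m = 4.5; equal total variance in both arms; a single post-baseline contrast.

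**Number of groups.** 25/5 = 5 and 25/4 = 6.25, so about 5–6. This is inferred, not stated.

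**Step 1: the plan's own figure.** With 21 per arm and power 0.80, difference/SE = 1.960 + 0.842 = 2.802. The implied SD of change is 5 / (2.802 × √(2/21)) = 5.78. No SD is given, so the 42 can be neither confirmed nor refuted (SD 5 would need 32 in total, SD 6 would need 46). The steps below need no SD. They take 42 children as giving 0.80 under independence and ask what clustering does to that.

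**Step 2: variance.** The design effect in the intervention arm is DE = 1 + (m − 1) × ICC. The control arm has DE = 1. With equal arms, the variance of the difference is multiplied by V = (DE + 1)/2, and the true SE is √V times the child-level SE.

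**Step 3: consequences.**
- Type I error of the child-level test = 2 × [1 − Φ(1.960/√V)].
- Power of a test with the correct SE, 42 children = Φ(2.802/√V − 1.960).
- Power of a test with the correct SE, 50 children = Φ(2.802 × √(25/21)/√V − 1.960) = Φ(3.057/√V − 1.960).
- Total needed for 0.80 = 42 × V.

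| ICC | DE | V | √V | Type I error | Power, 42 | Power, 50 | N for 0.80 |
|---|---|---|---|---|---|---|---|
| 0 | 1.000 | 1.000 | 1.000 | 5.0% | 0.800 | 0.864 | 42.0 |
| 0.01 | 1.035 | 1.018 | 1.009 | 5.2% | 0.793 | 0.858 | 42.7 |
| 0.05 | 1.175 | 1.088 | 1.043 | 6.0% | 0.766 | 0.834 | 45.7 |
| 0.10 | 1.350 | 1.175 | 1.084 | 7.1% | 0.734 | 0.805 | 49.4 |
| 0.20 | 1.700 | 1.350 | 1.162 | 9.2% | 0.674 | 0.749 | 56.7 |

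Worked line, ICC 0.10: DE = 1 + 3.5 × 0.10 = 1.35; V = 2.35/2 = 1.175; √V = 1.084; 2.802/1.084 − 1.960 = 0.625; Φ(0.625) = 0.734.

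**Step 4: group size.** Moving m from 4 to 5 at ICC 0.10 changes power at 42 from 0.743 to 0.725, and at 50 from 0.813 to 0.797.

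**Step 5: where the margin of eight children runs out.** 50 analysed children give 0.80 when V = 50/42 = 1.190, that is ICC = 2 × 0.190/(m − 1): about 0.13, 0.11 and 0.10 for m = 4, 4.5 and 5.

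**Step 6: check by simulation.** With 25 per arm, a t reference and n − 1 variances, so that clustering is the only fault, the type I error was about 6.0%, 6.9% and 9.1% at ICC 0.05, 0.10 and 0.20. A partially nested test at training-group level with Satterthwaite degrees of freedom held about 5%.

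**The case against.** The strongest reply is that everything turns on an ICC the article does not give. At ICC 0 there is no problem, and at 0.01 it is negligible. The article also offers reasons for a modest value: load is set from each child's own 8 RM, and the high-load stations are supervised one to one. This stands in part. It rules out unconditional wording, but it does not make the ICC zero, and the article presents the group as part of what makes the training work.

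It can also be said that randomisation within school deals with the hierarchy. It does so for schools, where both arms are drawn from each site. It does not do so for training groups, which exist in one arm only.

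A reader might go further and infer any of the following. None is supported.
- **That the GEE uses uncorrected large-sample standard errors.** The article states no type of standard error, reference distribution or small-sample correction, and a condensed article may leave these to the full plan.
- **That a joint test over the three visits is planned, with greater inflation.** The article says only that the group-by-time interaction is used.
- **That drop-out will bias the GEE because it must be completely at random.** Expecting some drop-out says nothing about its mechanism, and the handling of missing data may be set out elsewhere.
- **That group membership was fixed for all 12 weeks.** This is plausible but not stated.

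**Conclusion.** The point holds conditionally. The dependence named for the GEE omits the training group, and the stated reason for the sample size margin omits it too. If outcomes correlate within training groups, the standard error of the group-by-time effect is about 4%, 8% or 16% larger than a child-level analysis allows for, at assumed ICC 0.05, 0.10 or 0.20. The corresponding type I error is about 6%, 7% or 9%. Power at 42 is about 0.77, 0.73 or 0.67, on the premise that 42 gives 0.80 under independence.

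Two limits apply. A reader might conclude that the stated 0.8 is wrong; without an SD and an ICC it can only be shown to be sensitive, not wrong. A reader might also conclude that the drop-out margin is already spent. With all 50 analysed, power stays at about 0.80 or more up to an ICC of about 0.10, so the margin absorbs either that much clustering or the drop-outs, but not both. The Abstract reports 51 recruited, which changes little.

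The power figures use a normal approximation. With only 5–6 groups, the lower degrees of freedom of a correct analysis would cost somewhat more.

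**What to change.** - Record the training group of each intervention child, and note any change of group during the 12 weeks.
- Fit a partially nested model, either as the primary analysis or reported beside the GEE: a random training-group effect in the intervention arm only, controls as singletons, a within-child covariance for the repeated measures, and Satterthwaite or Kenward–Roger degrees of freedom.
- In the Sample size section, give the SD behind the 42, and the power for 42 and for 50 children over a stated ICC range, labelled as an assumption.

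The cost is one extra variable per intervention child and a few sentences; the Data-analyses section is still written in the future tense. No new outcome data are needed. The price is slightly wider intervals and a group variance estimated from few groups. That estimate will be imprecise, so the small-sample degrees of freedom are a necessary part of the change.
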